### Type of trial

This is a prospective, randomized, interventional, patient-blinded single center trial with two parallel comparison groups.

#### Randomization

To achieve comparable groups in terms of known and unknown risk factors, randomization will be performed. The allocation schedule will be generated by computer-generated random numbers, with an allocation ratio of 1:1 equal probability of assignment to each group. All patients will be randomized using consecutively numbered opaque envelopes sealed by the investigators. Envelopes will be opened upon entrance of the patient to the operating room.

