**Methods/Design:**

This study will include patients 18 years and older scheduled for hepatectomy with hepatic vascular exclusion who give informed consent. A sample size of 48 patients in each randomization arm will be calculated to detect a difference in the reduction of blood loss of approximately 200 ml (90% power and α = 0.05 (two-tailed)). The primary efficacy endpoint of the trial will be the total intraoperative blood loss based on the randomized dissection technique. The statistical analysis is based on the intention-to-treat population. Patients will be followed up on for three months for complications and adverse events.

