### Patient involvement

The sample size is based on a two-sided t-test for differences with respect to the primary parameter and primary analysis. In a retrospective analysis of our own series, the mean intraoperative blood loss was 450 ml those who underwent BiClamp forceps liver resection, with a standard deviation of 350 ml [14,15]. With a two-sided level of significance α = 5% and a power of 1-β = 90%, a sample size of 43 patients in each group is required to detect a difference in the reduction of blood loss of approximately 200 ml (NCSS and PASS 11 (NCSS, Utah, USA). Assuming an expected withdrawal rate of 10% during the trial, 10 additional patients will be randomized, and a total number of 96 patients need to be enrolled (Figure 1).

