### Eligibility criteria

#### Inclusion criteria

Patients who meet the following criteria will be included in the study:Above 18 years of age,Elective hepatic resection due to benign or malignant hepatobiliary disease,Child-Pugh class A or B liver function andInformed consent.

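### The primary ANCOVA adjusts for resection extent only through an area traced after allocation and omits Child-Pugh class, and the allocation as described names no stratum for either

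*Protocol article*

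**What the plan says.** All references are to the protocol article.

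- **Eligibility.** The inclusion criteria admit elective resection for benign or malignant disease with "Child-Pugh class A or B liver function". The exclusion criteria remove laparoscopic resection and Child-Pugh C, and set no limit on extent.
- **Allocation.** The Randomization section gives its purpose as "To achieve comparable groups in terms of known and unknown risk factors, randomization will be performed". It describes a computer-generated schedule "with an allocation ratio of 1:1 equal probability of assignment to each group", held in sealed numbered envelopes that are opened when the patient enters the operating room. It mentions neither strata nor blocks. The abstract gives "A sample size of 48 patients in each randomization arm".
- **Blinding.** Patients and outcome assessors are blinded. The surgeon cannot be, and one surgeon performs every operation (Standardization of perioperative care).
- **Endpoint and model.** The primary endpoint is total blood loss in ml from incision to skin closure. Statistical analysis specifies an ANCOVA on four covariates: transection surface area, CVP, preoperative INR and preoperative platelet count. Table 1 says the area is traced on paper when the resection is finished.

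**The concern.** Total blood loss in ml can be expected to rise with the size of the resection. The plan treats it so: it adjusts for transection area and makes blood loss per unit area a secondary endpoint. Liver function is a second plausible driver, and eligibility lets it vary.

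Both planned extent and Child-Pugh class can be known before the envelope is opened, yet neither is named as a stratum or entered in the primary model. The model handles extent through one variable, and that variable comes into being after allocation, during an operation whose arm the surgeon knows. If technique, or knowledge of the arm, changes where or how the liver is divided, the area is partly an outcome. Adjusting for it could then absorb or distort some of the treatment effect. Of the four covariates only INR and platelets are labelled preoperative.

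At stake are precision and the protection of the adjusted estimate, not the validity of the randomisation.

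**Working it through.** **Inputs from Patient involvement.** Difference 200 ml ("to detect a difference in the reduction of blood loss of approximately 200 ml"); SD 350 ml ("with a standard deviation of 350 ml"), taken as common to both arms; two-sided 5%; 90% power; t-test; 43 per group; 10% withdrawal; 96 in total.

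**The plan's own figure.** n per arm = 2 × 350² × (1.960 + 1.282)² / 200² = 64.4, so 65 (66 with the exact t-test). The stated 43 is not reproduced. The withdrawal step is: 43 / 0.9 = 47.8, so 48 per arm and 96 in total. The shortfall is a separate matter. It is noted here because it makes the baseline power at 48 per arm 79.1% (exact t-test, SD 350), not 90%.

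**Step 1: arm sizes, if the list were unrestricted.** With Binomial(96, 0.5):
- P(48/48) = 8.1%
- P(arms differ by 10 or more) = 35.8%
- P(an arm below 43) = 26.1%

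Average power over these splits is 78.7%, against 79.1% at 48/48. The cost is 0.4 points. At an SD of 286 ml, the value that would give 43 per group, it is 92.1% against 92.4%.

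**Step 2: chance imbalance in extent.** The share of major resections is not given, so 20% to 40% is assumed.

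| Major resections | Gap of at least 10 points, simple allocation | Same, fixed 48/48 without strata |
|---|---|---|
| 20% | 22% | 31% |
| 30% | 30% | 37% |
| 40% | 32% | 30% |

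Fixing the arm sizes does not cure this. Only a stratum or a baseline covariate addresses it. (Counts are whole patients, so the two columns do not rank consistently.)

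**Step 3: size of the shift.** Shift in the raw difference = imbalance × extra loss per major resection. For a 15-point gap and 200 to 500 ml (assumed), it is 0.15 × 200 = 30 ml to 0.15 × 500 = 75 ml. The standard error of the raw difference is 350 × √(2/48) = 71 ml. Even the largest shift is about one standard error.

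**Step 4: precision from a baseline extent term.** Share of variance explained = p(1 − p)d² / 350², where p is the share of major resections and d their extra loss. Residual SD = √(350² − p(1 − p)d²). Power is the exact t-test at 48 per arm.

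| p | d (ml) | Variance explained | Residual SD (ml) | Power |
|---|---|---|---|---|
| none | none | 0% | 350 | 79% |
| 20% | 200 | 0.16 × 40,000 / 122,500 = 5% | 341 | 81% |
| 40% | 200 | 0.24 × 40,000 / 122,500 = 8% | 336 | 82% |
| 20% | 500 | 0.16 × 250,000 / 122,500 = 33% | 287 | 92% |
| 40% | 500 | 0.24 × 250,000 / 122,500 = 49% | 250 | 97% |

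These are gains over an unadjusted test. The gain over the planned ANCOVA is smaller, by whatever transection area or INR already carries, and the documents do not allow that part to be computed.

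**Step 5: cost of the extra terms.** Two fewer error degrees of freedom at an SD of 350 ml lower power from 79.12% to 79.11%.

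**The case against.** Much of the opposing case stands.

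- A reader might infer that the trial uses unrestricted coin-toss allocation and therefore fails to deliver 48 per arm or comparable groups. The text does not support that. It never calls the list simple or unrestricted. A prepared 1:1 schedule is compatible with a fixed or blocked list, and each patient has equal probability of either arm under permuted blocks too. A condensed article commonly leaves such detail to the full protocol.
- Even if allocation were unrestricted, Step 1 shows that the arm-size consequence is negligible.
- Unstratified randomisation is unbiased and keeps the type I error. The comparability sentence states an aim, which is met in expectation. The 350 ml SD is not described as within a level of extent, so ordinary imbalance in extent is already in the standard error.
- Transection area is a continuous measure of size, finer than a major/minor split. It will probably take up much of the extent effect. INR and platelets are preoperative and bear on liver function and bleeding risk.

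The last point does not fully answer the concern. Area is not a baseline factor: it is measured after the surgeon knows the arm, and nothing in the document shows that it is unaffected by technique. INR and platelets do not record Child-Pugh class. The covariate list is a stated choice, not a detail left for later.

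**Conclusion.** The point holds for the primary model. As described, neither allocation nor analysis uses a pre-randomisation measure of extent or Child-Pugh class, and the only extent term is post-allocation.

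The gain in power over an unadjusted test runs from about 2 points (79% to 81%) to about 18 points (79% to 97%). It rests on two assumptions absent from the documents (20% to 40% major resections, 200 to 500 ml extra loss) and on an SD of 350 ml in both arms. The true gain over the planned ANCOVA is smaller by an unknown amount. No gain is computed for Child-Pugh class, because its frequency and effect are not given.

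The point does not show bias from the randomisation, a failed allocation or a material loss of power from unequal arms. It is a worthwhile and nearly free improvement to the primary analysis.

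**What to change.** In Statistical analysis, add two pre-randomisation covariates to the primary ANCOVA for all patients:

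1. preoperatively planned extent (major versus minor), recorded at Visit 1, or taken from preoperative records for patients already enrolled;
2. Child-Pugh class (A versus B), which the eligibility check already establishes.

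Adjustment for extent then no longer rests on a post-allocation measure alone. While transection area stays in the model, its post-allocation character stays with it.

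The cost is one Visit 1 item, a review of preoperative records for patients already enrolled, and two degrees of freedom. Both terms should be fixed before outcome data are compared by arm.

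Stratified permuted blocks of varying size for the remaining patients are optional. They would improve balance on planned extent. Against that, enrolment started on 1 October 2014, so the list would change mid-trial, and blocks make some assignments more predictable to a single unblinded surgeon.

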#### Withdrawal

Patients can withdraw at their own request or at the legal representative’s request at any time during the trial. Patients may also be withdrawn if, in the investigator’s opinion, continuation of the trial may be detrimental to the patient’s wellbeing. The reason for all withdrawals will be recorded in the clinical report forms (CRFs) and in the patient’s medical records. All data will be analyzed according to the intention-to-treat (ITT) principle [16].

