#### Blinding

Patients and outcome assessors will be blinded to the trial intervention. Blinding of the surgeons and people in the operation is not feasible due to the nature of the interventions.

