### Standardization of perioperative care

The operations will be performed by one senior surgeon ([name]) who is equally skilled in both the BiClamp forceps and clamp crushing techniques. Except for the trial interventions, perioperative care will be standardized in both study groups following the guidelines of the Department of General Surgery at the Second Affiliated Hospital of Anhui Medical University. In addition, all resections will be performed with the requirement of a low CVP (0 to 5 mm Hg) and an intermittent Pringle maneuver (periods of 15 minutes of clamping and 5 minutes of unclamping).

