**Table 2 Tab2:** **Flowchart of the trial**

	**Screening**					
	**Visit 1 Before surgery**	**Visit 2 Day of surgery**	**Visit 3 (POD1)**	**Visit 3 (POD3)**	**Visit 3 (POD7)**	**Visit 4 (POD90)**
Selection criteria and informed consent	×					
Medical history demographics	×					
Physical examination	×					
Laboratory tests	×		×	×	×	×
Trial intervention		×				
Intraoperative outcomes		×				
Postoperative outcomes			×	×	×	×

POD: postoperative days.

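### Allocation concealment is not assured: the investigators seal the numbered envelopes, and no independence from enrolment or surgery is stated

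*Protocol article*

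**What the plan says.** All references are to the protocol article.

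- **Randomization, sequence:** "The allocation schedule will be generated by computer-generated random numbers", "with an allocation ratio of 1:1 equal probability of assignment to each group". No blocks or strata are mentioned.
- **Randomization, implementation:** "All patients will be randomized using consecutively numbered opaque envelopes sealed by the investigators".
- **Randomization, disclosure:** "Envelopes will be opened upon entrance of the patient to the operating room".
- **Table 2 (trial flowchart):** the row "Selection criteria and informed consent" is ticked at Visit 1, before surgery, so entry is decided before the envelope is opened.
- **Withdrawal:** "Patients may also be withdrawn if, in the investigator’s opinion, continuation of the trial may be detrimental to the patient’s wellbeing". The same section has all data analysed by intention to treat.
- **Data management and quality assurance:** an independent study doctor with no part in care in the operating room completes the CRF. The article gives this role no part in randomization.
- **Statistical analysis:** the primary test is an ANCOVA adjusting for transection surface area, CVP, preoperative INR and preoperative platelet count.

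**The concern.** Concealment means that nobody who can affect whether, when or in what order a patient enters the trial knows the next assignment. A person who prepares numbered envelopes can know which arm lies behind each number. Assigning the sealing to the investigators, with no separation of roles stated, leaves open the possibility that such knowledge sits inside the team that enters patients or operates.

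The comparability of the two arms is at stake, and that is the section's own reason for randomizing. With foreknowledge, a patient expected to bleed heavily could be deferred, passed over or moved in the order. The risk would also have a likely direction. The Discussion reports that the team's retrospective data favour BiClamp, and the Background presents the trial as a means of confirming its superiority.

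**Working it through.** The article states no figure on this point, so the check consists of setting the sections side by side, followed by one labelled illustration.

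**1. Whom do the stated safeguards protect against?** Numbering, opacity and sealing stop someone without access to the contents from reading or reordering assignments. Opening in the operating room delays disclosure until after consent. None of these removes knowledge already held by whoever prepared the envelopes.

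**2. Is that person kept apart from enrolment and surgery?** The Randomization section names the investigators. The Withdrawal section ties a decision about individual patients to the investigator. Independence is specified only for data entry. No section separates the sealers from those who select patients or operate.

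**3. Could foreknowledge be acted on?** Surgery is elective (Inclusion criteria), and lack of compliance is a discretionary exclusion (Exclusion criteria). Trial status gives about 80 hepatectomies a year and about 20 months of recruitment: 80 × 20/12 ≈ 133 operations. Even if all 96 planned patients come from these, 133 − 96 = 37 would not enter. There is room for selection; this does not show that selection occurs.

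**4. Would the analysis repair it?** Intention to treat keeps patients in the arm assigned but does nothing about selection before assignment. The ANCOVA can absorb selection only as far as it works through its four covariates. Any other predictor of bleeding that can be judged beforehand stays unadjusted.

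**5. Illustration of scale (hypothetical, unadjusted).** Suppose k patients, each expected to bleed d ml more than average, end up in the clamp-crushing arm instead of the BiClamp arm, in exchange for k average patients. With n per arm, the BiClamp mean falls by kd/n and the other mean rises by kd/n, so the difference shifts by 2kd/n. From the article, n = 48, the target difference is 200 ml, and the SD is 350 ml (from the BiClamp series). The values of k and d are assumptions.

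| k | d (ml) | Shift = 2kd/48 (ml) | Share of 200 ml |
|---|---|---|---|
| 1 | 350 (1 SD) | 2 × 1 × 350/48 = 14.6 | 7% |
| 5 | 175 (½ SD) | 2 × 5 × 175/48 = 36.5 | 18% |
| 5 | 350 (1 SD) | 2 × 5 × 350/48 = 72.9 | 36% |

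The table shows how the shift scales under these assumptions. It does not estimate bias in this trial.

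**The case against.** A reader might infer that allocation is simply not concealed, and that the investigators who seal the envelopes also screen, consent and schedule patients. The text does not support this. It states real concealment measures, including opening only after entry and consent are settled. It does not say that the sealers fill the envelopes, hold the list, enrol patients or operate. Screening and consent are described without naming a role, and nothing says who schedules surgery; only withdrawal is tied to the investigator. This objection stands, and it limits the point to concealment that is not assured.

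Two other supports are weaker than they look. The article says "Blinding of the surgeons and people in the operation is not feasible due to the nature of the interventions" and "The operations will be performed by one senior surgeon". An unblinded operating team matters mainly after the envelope is opened, as performance bias, and does not show that assignments were known beforehand. A single surgeon may mean that cases pass through a small team, but that too is no evidence of foreknowledge. Withdrawal after assignment is also a poor route to bias when all data are analysed by intention to treat.

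It can fairly be said that a journal article leaves list custody and role separation to the full protocol, so their absence is no fault. That is right as far as it goes. The point rests instead on what the article does fix, namely that the investigators do the sealing.

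Lastly, patients expected to bleed heavily may differ partly in transection area, INR or platelets, so the ANCOVA could remove some of any shift. That also stands. It makes the illustration an unadjusted figure but does not make adjustment a substitute for concealment.

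**Conclusion.** The point holds in limited form. The stated procedure leaves concealment unprotected against the people who prepare the envelopes, and the article states no separation between them and enrolment or surgery. This is a risk of selection bias in the primary comparison, not a demonstrated breach. Its size cannot be estimated from the article; the illustrated shifts of about 15 to 73 ml depend wholly on the assumed number and severity of swapped patients.

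The conclusion rests on two readings: that sealing gives access to the assignments, and that the investigators are not a group kept apart from patient entry and surgery. If they were in fact kept apart, a sentence saying so would close the point. The change is worth making because it is cheap and because no later analysis can be counted on to undo the bias.

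**What to change.** In the Randomization section, replace the clause that has the investigators seal the envelopes. State instead that an existing staff member prepares, seals and keeps them, and that this person takes no part in screening, consent, surgery, outcome assessment or CRF entry. The independent study doctor who completes the CRF should therefore not take on this task.

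Enrolment began on 1 October 2014, so patients already randomized keep their assignments. The unused envelopes should be withdrawn and re-prepared by the new custodian from a fresh computer-generated list at the same 1:1 ratio. Patient number, date and time are written on each envelope before it is opened and entered in a log, so that the order of use can be audited.

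The cost is one reassigned clerical task and a log sheet. Sample size, interventions, visits and primary analysis are unchanged.

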### Statistical analysis

The two-sided null hypothesis for the primary outcome measure states that both study interventions lead to similar total intraoperative blood loss; the alternative hypothesis is that one intervention performs better than the other. This null hypothesis will be tested by application of an analysis of covariance that adjusts for the transection surface area, CVP, preoperative international normalized ratio (INR) and preoperative platelet count.

Background characteristics and surgical outcome measures will be compared using Fisher’s exact tests or chi-squared for categorical data, and Student’s t-test for continuous variables. Categorical data will be presented as frequencies and group percentages, and continuous variables will be expressed as the means and standard deviations. The homogeneity of the two groups will be described by comparing the demographic data and baseline values. All analyses will be performed on an ITT basis [16]. For the ITT analysis, data will be processed for all trial patients in the groups in which they are randomized. Statistical significance is defined as *P* <0.05. All statistical calculations will be performed with the help of SPSS10.0 (SPSS, Chicago, USA).

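### Opening the envelope at theatre entry, before exploration, sets the ITT rule against the primary ANCOVA for any unresected patient and lets the resection be settled with the arm known

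*Protocol article*

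**What the plan says.** All places are in the protocol article.

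- **Randomization.** Allocation is 1:1 from a computer-generated schedule, held in "consecutively numbered opaque envelopes sealed by the investigators". On timing: "Envelopes will be opened upon entrance of the patient to the operating room".
- **Trial interventions.** Groups A and B are described only by how the parenchyma is divided and how vessels and ducts are dealt with during that division.
- **Blinding.** "Blinding of the surgeons and people in the operation is not feasible due to the nature of the interventions". Under Standardization of perioperative care: "The operations will be performed by one senior surgeon".
- **Inclusion criteria.** Entry rests on the indication: "Elective hepatic resection due to benign or malignant hepatobiliary disease". No step confirms resectability at exploration before the envelope is opened.
- **Primary endpoint.** Blood loss is counted from skin incision to skin closure.
- **Statistical analysis.** The primary test is an ANCOVA with four covariates: transection surface area, CVP, preoperative INR and preoperative platelet count. Under ITT, "data will be processed for all trial patients in the groups in which they are randomized".
- **Table 1.** Transection area comes from a tracing of the transection plane made when the resection is finished.
- **Patient involvement.** The only allowance for loss is this: "Assuming an expected withdrawal rate of 10% during the trial".

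**The concern.** Neither technique is used until transection begins, so neither needs the allocation to be known at theatre entry. Revealing it that early has two consequences.

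1. **The ITT rule and the primary model can collide.** A patient randomised at theatre entry but not resected belongs to the ITT population and has a value for the primary endpoint. One covariate of the primary model has no value for that patient as it is defined. The analyst must remove a randomised patient or assign an area of zero. Removal breaks the stated rule. A zero keeps in the comparison a patient who received neither technique, and it relies on the fitted area slope holding down to zero.

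2. **A primary-model covariate is settled after the arm is known.** The single surgeon knows the arm during exploration and mobilisation and when the final plane is chosen. The resulting area is then adjusted for. If the arm influences the extent of resection, that adjustment can bias the treatment contrast. Blood lost during mobilisation also counts in the endpoint, so handling at that stage can differ by arm and be recorded as a technique effect.

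A secondary matter is that the same section has investigators seal the envelopes and states no separation between that task and recruitment, surgery or outcome assessment.

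**Working it through.** **1. Order of events**

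| Event | Where fixed | Arm known? |
|---|---|---|
| Selection and consent, before surgery | Table 2 | No |
| Envelope opened at theatre entry | Randomization | From here on |
| Skin incision; blood-loss count starts | Primary endpoint | Yes |
| Exploration, mobilisation, final plane | Not described | Yes |
| Transection, where the arms differ | Trial interventions | Yes, unavoidably |
| Plane traced; area obtained | Table 1 | Yes |
| Skin closure; count ends | Primary endpoint | Yes |

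Opening the envelope just before transection would change the entry to No for incision, exploration, mobilisation and the choice of plane. It would change nothing later.

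**2. A randomised but unresected patient**

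- Primary endpoint: defined (incision to closure).
- Transection area: no plane, so no tracing and no value as defined.
- ITT: the patient must be analysed in the allocated arm.
- Result: the patient is dropped (ITT broken) or given area 0 (a convention the article does not provide). Transection speed and blood loss per unit area remain undefined either way.

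**3. Effect on power**

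Inputs from Patient involvement: difference 200 ml, SD 350 ml, two-sided 5%, 43 evaluable per group, 96 in total, so 48 per arm. The unresected share *u* is not in the documents; I assume 3%, 5% and 10%.

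The plan's own figure first: 43 / (1 − 0.10) = 47.8, so 48 per arm and 96 in total, which agrees. The 43 itself does not reproduce. A two-sided t-test with these inputs and 90% power needs 65.3, so 66 per group. That is a separate issue, and this point does not depend on it. It does mean that the baseline here is 79%, not 90%.

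Formula: noncentrality = (Δ/SD) × √(n/2), with 2n − 2 degrees of freedom and power from the noncentral t.

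Baseline: (200/350) × √(48/2) = 2.80, power 79.1%.

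*Kept in ITT with no arm difference.* The effect becomes 200 × (1 − u); n stays at 48 and SD is held at 350:

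| u | Effect (ml) | Power |
|---|---|---|
| 3% | 194 | 76.7% |
| 5% | 190 | 74.9% |
| 10% | 180 | 70.3% |

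*Dropped.* The effect stays at 200 ml; n becomes 48 × (1 − u):

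| u | n per arm | Power |
|---|---|---|
| 3% | 46.6 | 77.9% |
| 5% | 45.6 | 77.0% |
| 10% | 43.2 | 74.7% |

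These figures assume no other loss. If the 10% withdrawal allowance is also used up (43 per arm), power starts at 74.5%, and a 10% dilution takes it to 65.4%.

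The loss is therefore 2 to 9 percentage points if such patients are kept and 1 to 4 if they are dropped. The possible bias from adjusting for an area settled after allocation cannot be sized from the documents.

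**The case against.** The strongest reply is that the article never mentions an unresectable patient. These are elective, planned resections, and the frequency may be small. Such a patient has a blood-loss value, zero is arguably a literal measurement of the area, and the handling of randomised but untreated patients is commonly left to an analysis plan, which is not shown. Low CVP and intermittent Pringle clamping are required for all resections. The surgeon must know the arm during transection whenever the envelope is opened. And enrolment began on 1 October 2014, so a change now would mix two randomised populations.

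Much of this stands and limits the point:

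- A reader might infer that unresected patients will certainly occur, or at 10%. The documents give no rate, and the 10% in the sample-size section is for withdrawal.
- A reader might infer that such patients cannot enter the ANCOVA at all. They can if the area is set to zero; they cannot with the covariate as defined.
- A reader might infer that CVP management will drift by arm. The common CVP requirement narrows that possibility, and nothing shows a difference.
- A reader might infer that the surgeon decides the extent of resection only after seeing the allocation. The text shows only that no recorded plan prevents it.
- A reader might infer that the sealing investigators know the sequence. The text does not say so; it states only no separation of roles.

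What the reply does not remove is the stated timing. A later analysis plan could settle how unresected patients are handled, but it could not undo disclosure of the arm before exploration. The mid-trial objection bears on how the change is made, and the amendment can deal with it.

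**Conclusion.** The point holds as an improvement to a stated rule. Opening at theatre entry reveals the arm earlier than either technique requires. It creates a possible conflict between ITT and the primary ANCOVA, and it lets mobilisation and final extent, and with them a primary-model covariate, be settled with the arm known.

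Its size in power terms is modest: from about 79% to 77-70% if unresected patients are kept, or to 78-75% if they are dropped. This rests on an assumed 3% to 10% unresected, equal shares in both arms, no arm difference among those patients, SD held at 350 ml and 48 per arm with no other loss. Most of the gap to the stated 90% has another cause, the sample size of 43. The case for change is the avoidable risk of bias and an ITT rule that the model may be unable to honour. The documents do not show that either has occurred. The sealing of the envelopes is a secondary point of clarification.

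**What to change.** 1. Amend Randomization so that the envelope is opened in theatre only after resectability is confirmed and the planned resection recorded, immediately before parenchymal transection.
2. Keep the primary endpoint as it is, counted from skin incision. Blood lost before opening then precedes allocation, so it cannot be influenced by the arm and differs between arms only by chance.
3. Because enrolment has started, record the date of the change, identify patients randomised before and after it, and report a sensitivity analysis by randomisation period.
4. State that existing staff with no role in recruitment, surgery or outcome assessment prepare and seal the envelopes.

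The cost is a short amendment and one extra sensitivity analysis. In theatre, both instrument sets must be ready and there is a short wait for the envelope. The sample-size calculation is unchanged by this amendment.
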